**Safety of XAV-19 evaluated as:**

- Occurrence of all suspected XAV-19 related adverse effects or Incidence of serious adverse events
- Study drug discontinuation or temporary suspension of infusion
- Proportion of participants with treatment emergent adverse events leading to study drug discontinuation
- Incidence of major or opportunistic bacterial or fungal infections
- Incidence of hypersensitivity reactions and infusion reactions
- White cell count, hemoglobin, platelets, creatinine, ALT, AST, on D1, D3, D5, D8, D15 and D29

**Exploratory analysis**

- SARS-CoV-2 status (positive or negative and quantitatively, including variant information by sequencing) over time (D1, D8, D15, and D29)
- SARS-CoV-2 status viral load over time (D1, D8, D15, and D29)

## Objective and endpoints for ancillary studies for phase 2b

Three ancillary studies will complete the phase 2b. For the pharmacokinetic study, 90 patients will be included, as for the immunomonitoring study 100 patients will be included. Finally, at the end of phase 2b study, 20 patients will all receive 150mg of
XAV-19. Analyses performed will be identical to those performed in the phase 2a study.

Study sites involved in these ancillary studies will propose to their first patients to participate to these studies. For the first two studies mentioned patients can participate simultaneously to both studies.

### Pharmacokinetic Study (90 patients)

#### Objective

The objective of the pharmacokinetic study is to characterize pharmacokinetics (PK) of XAV-19 infected patients over the time from D1 to D29.

#### Endpoint

Pharmacokinetic analysis correspond to antibody titer measurements at Day 1 (pre-dose, post-dose), Day 3, Day 5, Day 8, Day 15, and Day 29.

### Immunomonitoring Study (100 patients)

#### Objective

Objectives will be to assess the effects of neutralizing antibodies use on virus-induced immune response on longitudinal follow-up, and to identify targets for "immuno-monitoring" for the next phase of the study and to investigate the immunogenicity of COVID-19 during treatment with XAV19.

#### Endpoint

The endpoints encompass the following analysis:

- Spike/ACE2 neutralizing antibody titers: D1 (pre-, post dose), D3, D5, D8, D15 and D29
- Lymphocytes sub-population: D1, D3, D5, D8 and D15
- Transcriptomic analyses: D1, D3, D5, D8 and D15
- Cytokines: D1, D3, D5, D8 and D15

### Terminal ancillary Study (20 additional patients)

#### Objective

The objectives are:

-to compare pharmacokinetic parameters in patients receiving a fixed dose of 150mg with patients receiving 2mg/Kg of XAV-19 (master phase 2b), in order to confirm that the exposure and variability are similar

-to compare the effects of neutralizing antibodies use on virus-induced immune response on longitudinal follow-up, and targets for "immuno-monitoring"

-to investigate the immunogenicity of COVID-19 during treatment with XAV19 in patients receiving a fixed dose of 150mg with patients receiving 2mg/Kg of XAV-19

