The phase 2b will be a double-blind, placebo-controlled randomized study to assess clinical benefit and safety of the phase 2a selected dose of XAV-19 in 398 hospitalized adults with COVID-19 associated moderate pneumonia. Patient will be randomized to either XAV-19 or placebo in a 1:1 ratio and will receive a single dose based on the analysis of the Phase 2a study.

In addition to ancillary studies conducted during both parts of the study, a terminal ancillary open label study will be performed after completion of the main phase 2b part to assess a flat dose regimen of XAV-19.

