### Statistical justification of the number of inclusions

Phase 2 a:

As it is a Phase 2 a, the number of patients was determined according to relevant publications of phase 2a. It was decided to enrol two cohorts of 8 patients (6 treated patients and 2 matching placebo in each cohort).

Phase 2 b:

Assuming a true treatment diminution in clinical failure rate of 10% for XAV-19 added to SoC therapy compared to placebo added to SoC therapy where a rate of 20% is expected, a sample size of 398 randomized participants provides at least 80% power that the primary analysis will be statistically significant at the two-sided 5% significance level.

The 20 patients of the open-label ancillary terminal study (150 mg dose of XAV-19) will not be included in the primary analysis. Their pharmacokinetic characteristics and variability will be compared to the parameters of randomized phase 2b patients taking part in the ancillary pharmacokinetics ancillary study and immunomonitoring ancillary study.

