### Expected level of statistical significance

The degree of significance is set at 5%.

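### The flat-dose sub-study aims to confirm similar exposure and variability, but sets no criterion for similarity, and 20 patients cannot confirm similar variability

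*Combined protocol and SAP*

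**What the plan says.** Protocol 3.2.3 gives the first objective of the terminal ancillary study as comparing pharmacokinetic parameters after 150 mg with those after 2 mg/kg "in order to confirm that the exposure and variability are similar". Protocol 7.2.2 covers the analysis in one sentence: "Their pharmacokinetic characteristics and variability will be compared to the parameters of randomized phase 2b patients". The same sentence limits the comparators to people "taking part in the ancillary pharmacokinetics ancillary study and immunomonitoring ancillary study". Section 7.2.2 also states: "The 20 patients of the open-label ancillary terminal study (150 mg dose of XAV-19) will not be included in the primary analysis".

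The comparator comes from two sub-studies described in 3.2: "For the pharmacokinetic study, 90 patients will be included, as for the immunomonitoring study 100 patients will be included". On overlap: "For the first two studies mentioned patients can participate simultaneously to both studies". Phase 2b allocation is equal (1.3): "Patient will be randomized to either XAV-19 or placebo in a 1:1 ratio".

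The only criterion in the protocol is the general line in 7.2.3: "The degree of significance is set at 5" per cent. SAP 3.1 repeats 5%, two-sided, for all applicable tests. Protocol 3.2 also says that the ancillary analyses will match those of phase 2a, where 7.2.1 names a Kruskal-Wallis test and ANOVA models. The SAP mentions the terminal ancillary study only in its section on timing of the final analysis, to leave those patients out of the unblinding decision.

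**The concern.** To confirm that two regimens are similar is an equivalence conclusion. It needs a statement of how large a difference would still count as similar, and an interval narrow enough to exclude anything larger. The plan has neither. What it does have is a significance level and, by reference to phase 2a, methods that test for a difference. A small sample tends to give non-significant differences whether or not the regimens differ, so without another rule the report could present an inconclusive comparison as confirmation.

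At stake is what the sub-study may conclude about replacing weight-adjusted dosing by a flat dose. Variability matters most, because a change from weight-based to flat dosing changes how exposure depends on body weight.

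**Working it through.** **Is there a stated figure to reproduce?** Not for this sub-study: no power, precision or margin is given for n=20. (The main phase 2b size does reproduce: 20% against 10%, two-sided 5%, 199 per arm, power 0.800. It has no bearing here.)

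**Group sizes.** Flat dose: 20. Comparator: placebo patients have no XAV-19 kinetics, so the PK study contributes about 90/2 = 45 (95% binomial range 36 to 54). If the PK and immunomonitoring studies did not overlap and all patients were assayed, the ceiling would be (90+100)/2 = 95. Protocol 6.2.2 takes PK from the immunology samples after the first 20 patients, which suggests substantial overlap, so 45 is the main case.

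**Variability (no CV needed).** I use a two-sided 5% F test on log-exposure variances, assumed normal, with 19 and 44 df. The critical values are 0.432 and 2.052. For a true SD ratio R (flat over 2 mg/kg), the chance of missing it is 1 − P(F > 2.052/R²) − P(F < 0.432/R²).

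| True SD ratio | Missed, 20 v 45 | Missed, 20 v 95 |
|---|---|---|
| 1.25, flat more variable | 77% | 72% |
| 1.5, flat more variable | 43% | 34% |
| 1.25, weight-based more variable | 82% | 81% |
| 1.5, weight-based more variable | 51% | 45% |

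The 95% CI around an observed SD ratio of exactly 1 runs from 1/√2.052 = 0.70 to 1/√0.432 = 1.52 (0.73 to 1.49 with 95 comparators). Even the most favourable result therefore leaves a 50% larger SD possible.

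**Are such ratios plausible?** Protocol 1.3 gives a median weight of 77.3 kg with [72-98], which I read as the interquartile range. The SD of ln weight is then ln(98/72)/1.349 = 0.229. Let s be the log-SD under whichever regimen removes the weight effect, with s² = ln(1+CV²). The other regimen has variance s² + 0.229². At CV 20%, 30% and 40% the variance ratio is 2.33, 1.61 and 1.35, so the SD ratio is 1.53, 1.27 and 1.16. Which regimen is the more variable is open. The Cmax examples in 1.3 (75 µg/ml at 50 kg, about 30 at 120 kg) let exposure follow dose per kg, which makes flat dosing the more variable. The next paragraph of 1.3 says that distribution and elimination do not increase with weight, which reverses the direction.

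**Mean exposure (CV assumed).** Two-sided 5% t test on the log scale, true ratio 0.80, so |ln 0.80| = 0.223. SE = s·√(1/20+1/45) = 0.2687s; 63 df, critical value 1.998; noncentrality = 0.223/SE.

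| CV | s | SE | Noncentrality | Missed, 20 v 45 | Missed, 20 v 95 |
|---|---|---|---|---|---|
| 20% | 0.198 | 0.053 | 4.19 | 2% | 0.5% |
| 30% | 0.294 | 0.079 | 2.83 | 20% | 13% |
| 40% | 0.385 | 0.104 | 2.16 | 44% | 35% |
| 50% | 0.472 | 0.127 | 1.76 | 59% | 52% |

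The one hint at a CV is the half-life range of 5.5 to 13.9 days at 2 mg/kg (SAP 1.1). ln(13.9/5.5) = 0.927. Divided by the expected range of six or five normal values (2.534 or 2.326), this gives a log-SD of 0.37 to 0.40, a CV of about 38% to 41%. It describes half-life, not exposure, and rests on very few patients.

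**The case against.** A reader might infer that the protocol prescribes a 5% difference test and will treat non-significance as confirmation. It does not say so. No test is named, the 5% line covers the whole protocol, and the reference to phase 2a analyses may mean laboratory work. SAP 3.1 treats secondary objectives as exploratory, with effect sizes and confidence intervals; although the SAP does not reach this sub-study, that rule points towards estimation. This stands. But a purely descriptive comparison would also leave the word confirm without a criterion.

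A reader might also infer that flat dosing will prove more variable. Protocol 1.3 supports either direction, so only the low power is established, not the sign.

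Nor is the sub-study the only evidence for a flat dose. Section 1.3 also offers phase 2a concentrations, dose-per-kg arithmetic, volume and clearance data, and literature, and nothing makes adoption depend on these 20 patients. Section 1.3 also puts exposure at 6 to 15 times the neutralizing concentration across 50 to 120 kg, so a 20% shift in the mean is not shown to matter clinically.

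Finally, the comparator could exceed 45. The effect is modest, because the 20 flat-dose patients dominate the standard error.

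**Conclusion.** The point holds as a mismatch between aim and plan: 3.2.3 promises confirmation of similarity, and neither document says what would count as similar. For variability, the low power holds without assuming a CV and in either direction: a 1.25-fold SD difference is missed 72% to 82% of the time across the two comparator sizes. The figures assume log-normal exposure.

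For mean exposure, it would go too far to say that a real difference will often be missed. At a CV of 20% the comparison is adequate for a 20% shift; from about 30% upwards it is not. The documents do not say which applies.

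The primary efficacy result is unaffected. This is a minor point, confined to what an ancillary study may claim, and it takes no position on which dose is right.

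**What to change.** In protocol 3.2.3 and 7.2.2, with a short matching SAP section:

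- Replace the aim of confirming similarity by one of estimating the comparison.
- Report the flat/2 mg/kg geometric mean ratio for AUC, Cmax and Day 8 concentration with a 90% CI, from a log-scale model with unequal variances.
- Report the ratio of between-patient log-SDs with a 95% CI, and plot exposure against body weight in each group.
- Define the comparator set.
- State that a non-significant difference is not evidence of similarity, and that the groups are sequential and not randomised against each other.
- Use the word similar only if the intervals lie inside limits that the sponsor fixes and justifies on exposure-response grounds before seeing the data.

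The limits should not be chosen because n=20 can meet them. For illustration (simulation, 20 v 45, equal variances), limits of 0.70 to 1.43 on the mean ratio would accept a true 20% reduction 79% of the time at CV 20% and 51% at CV 30%. Limits of 0.80 to 1.25 hold that to about 5%, but with a true ratio of 1 they are met only 74%, 36% and 10% of the time at CV 30%, 40% and 50%.

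The cost is wording and a small analysis of data already planned, with no extra patients or samples. The sub-study may then end as similarity not shown, especially for variability, which is the honest reading of a sample this size.

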#### Endpoint

Antibody titer measurements IN SERUM at Day 1 (pre-dose, post-dose), Day 3, Day 5, Day 8, Day 15, and Day 29

The endpoints encompass the following analysis:

- Spike/ACE2 neutralizing antibody titers: D1 (pre-, post dose), D3, D5, D8, D15 and D29
- Lymphocytes sub-population: D1, D3, D5, D8 and D15
- Transcriptomic analyses: D1, D3, D5, D8 and D15
- Cytokines: D1, D3, D5, D8 and D15

# Study treatment

In this study, XAV-19 is the Investigational Medicinal Product (IMP), Xenothera will be responsible for providing XAV-19 to Nantes University Hospital.

## Description and mode of administration

### Product Characteristics

- Physical and chemical characteristics:

XAV-19 is a glyco-humanized swine polyclonal IgG antibody targeting SARS-CoV-2 spike Receptor Binding Domain (RBD). It is composed of IgG molecules with a molecular mass of 150 kilodaltons (kDa). Glyco-humanization refers to replacement of animal-type Gal alpha 1-3 galactose (alpha-Gal) and N-glycolylneuraminic acid (Neu5GC) glyco epitopes by terminal glyco-epitopes of the human type (Neu5AC sialylation). XAV-19 is produced by immunization of genetically-modified swine in which the alpha 1,3-galactosyltransferase (GT1) and the cytidine monophosphate N-acetyl hydroxylase genes have been knocked out. Immunization has been performed with a recombinant protein comprising the Receptor Binding Domain (RBD) of the SARS-CoV-2 spike molecule. Swine are bred under Defined High Health Status (DHHS) conditions, suitable to produce parenteral pharmaceutical substances. Glyco-humanization reduces immunogenicity, prevents allergy due to recognition of alpha-Gal moieties by anti-alpha-Gal IgE and prevents formation of immune complexes that might arise as a result of recognition by pre-existing anti-Neu5GC natural antibodies, such complexes potentially causing serum sickness. XAV-19 binds to and blocks S1-dependent viral entry into ACE-2 positive human cells. Because it is a swine antibody, IgG Fc domains of XAV-19 do not bind to human Fc receptors and therefore XAV-19 is predicted to not being able to elicit antibody-dependent enhancement, i.e. antibody-dependent promotion of entry of viral particles into Fc receptor-positive human cells.

- Formulation

The drug product is provided as a sterile solution in a single use.

XAV-19 is a novel investigational drug formulated in a buffered solution of phosphate-buffered saline containing 0.05% polysorbate. Each ampoule is filled with a target volume of 5.5 mL which includes a 10% overfill to allow an extractable volume of 5 mL drug product containing 25 mg of XAV-19 (5 mg/mL).

The drug product should be stored at 2-8°C and is stable at this temperature for at least 6 months for the Phase 2a and 12 months for the Phase 2b. The shelf-life will be extended when actual data will become available. Swine GH-pAbs are projected to be stable at 4°C for > 3 years.

### Administration

The drug product is intended to be slowly administered by IV infusion after dilution in a NaCl 0.9% bag. The dilution will be based on the patient weight and the dose must be administered using in-line filtration.

For Phase 2a, XAV-19 will be given:

- at the dose of 0.5 mg/kg intravenously (IV) on Day 1 (D1) and Day 5 (D5) (i.e., 2 injections in total) in group 1.
- at the dose of 2 mg/kg intravenously (IV) on Day 1 (D1) and Day 5 (D5) (i.e., 2 injections in total) for the first two patients and on D1 only (i.e., one administration) for the rest of the group, in group 2.

XAV-19 will be administered by slow intravenous infusion of 100 mL over at least 30 min but not to exceed 60 min, after dilution to the right concentration in sterile NaCl 0.9% pocket.

Timing of infusion will have to be between 9 am and 4 pm at Day 1, and, as much as possible, at the same time as in Day 1, for Day 5 if applicable.

For Phase 2b, XAV-19 will be given at the dose chosen from the Phase 2a intravenously (IV) on Day 1 (D1), i.e 2mg/kg.

XAV-19 will be administered by slow intravenous infusion of 100 mL over at least 30 min but not to exceed 60 min, after dilution to the right concentration in sterile NaCl 0.9% pocket.

Timing of infusion will have to be between 9 am and 4 pm at Day 1

Additional detailed information on dose preparation and administration will accompany the clinical drug supplies to the clinical study sites.

For the terminal ancillary study, XAV-19 will be given at a fixed dose of 150mg, as single infusion.

#### Dose adjustment

In the absence of serious or grade 4 adverse events deemed at least possibly related to study drug treatment, patients will complete their scheduled infusions as prescribed by protocol.

In the event of new safety findings, serious and unexpected toxicity potentially related to XAV-19, study drug administration should be interrupted, and in case, only 1 dose has been administered, the second dose if applicable will not be administered (no dose adjustment). The investigator must immediately notify the adverse event/ new safety finding to the sponsor.

#### Reference documents

To date, no serious adverse reactions are considered expected for the purpose of expedited reporting of suspected unexpected serious adverse reactions (SUSARs).

For more information on the safety profile of XAV-19, please refer to the current version of the Investigator Brochure; section RSI (Reference Safety Information).

### Other study treatments

No other study treatment will be administered in the study.

## Treatment compliance follow-up

All medications specified in this protocol must be administered as described within the protocol.

The administration of XAV-19 must be done in the investigational site and supervised by a physician or a nurse of the department. The investigator and/or the pharmacist must retain adequate and accurate records of XAV-19, showing the receipt and distribution of the clinical supplies, and any deviations from specified administration should be clearly documented in the patient record.

## Experimental drug circuit

### General circuit

Labelled XAV-19 vials (IMP) are provided by Xenothera to Nantes University Hospital Pharmacy. Each vial contains 25 mg of XAV-19. Each ampoule is filled with a target volume of 5.5 mL which includes a 10% overfill to allow an extractable volume of 5 mL drug product containing 25 mg of XAV-19 (5 mg/mL).

Nantes University Hospital Pharmacy will manage XAV-19 vials: receipt, storage, relabelling (if applicable), distribution to the other sites hospital pharmacies or dispensing directly to investigational site (Nantes Hospital), accountability, and disposal (after sponsor approval).

The other sites hospital pharmacies will manage XAV-19 vials: receipt, storage, relabelling (if applicable), dispensing directly to investigational site, accountability, and disposal (after sponsor approval).

Each pharmacy will ensure IMPs reconciliation and accountability.

XAV-19 will be diluted in an infusion bag containing a variable volume (weight-dependent) of NaCl at the concentration of 0.83 mg/ml for groups 1 and 2 by each pharmacy department upon request of the investigational site.

The XAV-19 infusion bag will then be transferred to the investigational site for administration to the patient.

### Experimental drug storage conditions

The investigator (or the Hospital Pharmacy_PUI) is responsible for the safe storage of all study drugs assigned to the clinical site, in a secure place with restricted access, and maintained within the appropriate ranges of temperature.

Regular temperature logging of the study drug storage room should be performed. In case of temperature excursion during storage conditions, the pharmacy/site must notify immediately the sponsor. The pharmacy/site must wait for Sponsor approval, according to Xenothera’s recommendations, to dispense the affected study drug.

#### Description of dispensary storage

As of reception by the Hospital Pharmacies, IMPs are kept in a cool dry place, protected from light, where the temperature stays between +2 and +8°C.

The vials will be stored in a secured place whose temperature is monitored, stored away from conventional drugs.

#### Description of department storage

Once reconstituted in the NaCl bags, the pharmacy ensures the dispensing of IMPs to investigator’s team. XAV-19 pocket will be stored in the investigator site between +2 and +8°C until administration. Bags should be administered within 72h after reconstitution. Empty bags will be destroyed at clinical site.

### Unblinding procedure

Under normal circumstances, blind should not be broken until all patients have completed the study and the database is locked.

Phase 2b :

For the first set of statistical analyses, to allow early reporting of primary and secondary endpoints at D15, the blind will be partially broken once all patients have completed Day 29. Except for statisticians, only the principal investigator and the scientific coordinator will have access to the full data set for the analysis of the primary and secondary endpoints up to day 29. The database will be partially locked (with all data up to day 29) as neither monitors nor investigators will be informed of the unblinding until the final data for day 60 is completed and the final database is locked.

In the current study, the investigator does not need to know the treatment arm of the patient in case of adverse event, as the treatment will be symptomatic and not adapted to the arm. The blind will be broken only by the pharmacovigilant team for safety purposes and transmission.

This will be done according to the internal sponsor’s procedure.

For the terminal ancillary study, the study will be conducted as open label.

## Authorised and unauthorised treatments

### Authorised treatments

Standard of Care (SOC) for COVID-19 is defined by use of dexamethasone and per local practice and/or local/national guidelines at time of the study, which may include, not exclusively, antibiotics, antiviral treatment, corticosteroids, immune therapies not based on antibodies administration, anticoagulants.

